### 4.2 General Statistical Approach

**Primary analysis.** Baseline variables and outcome measures will be examined using descriptive and graphical displays such as boxplots and scatter plots. Appropriate transformations will be applied to data that is non-parametric. The primary analysis will be an unadjusted one-way ANOVA for fold-change in Nrf2 expression and phase II antioxidant levels with sulforaphane dose as the main effect. Post-hoc comparison between doses will use Tukey's test. Dose-response relationships will be tested with a test for trend (Pearson's  $r$ ). If significant imbalance occurs between groups, then general linear models will be constructed to adjust for baseline differences. The primary analysis will use the modified intention to treat paradigm.

**Secondary analyses.** Secondary outcome measures will be similarly analyzed, but p-values will be adjusted for multiple comparisons. Subgroups of interest (gender, smoking status, GOLD stage, adherent participants) will be examined by tests of treatment by subgroup interaction.

**Early stopping rules.** We are not proposing any interim efficacy analysis or early stopping rules.

Participants will continue to be enrolled in the trial regardless of whether they take the study medication, as our first analysis will be an intention to treat analysis. Secondary analyses will

include only adherent patients. Patients may be removed from the study if they sustain interim adverse events related to the study, if they are not healthy enough to undertake the study procedures (e.g. bronchoscopy).

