#### **2.5.1 Primary outcome**

1. Nrf2 levels and downstream anti-oxidants The primary design variables are the change in Nrf2 expression in alveolar macrophages (AM) and bronchial epithelial cells (BEC). Support of antioxidant effects will be quantified by changes in phase II anti-oxidant gene expression (NQO1, HO-1, GPX2, GCLM, GCLC, GSTA1). We will correlate changes in these levels with non-invasive measures from peripheral blood monocytes and nasal epithelial cells.

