## 4 Statistical Design and Sample size

### 4.1 Justification of Sample size

**Power Analysis:** For a one-way ANOVA, assuming 30 samples per each of 3 groups, and 80% power, the detectable effect size by Cohen's  $f$  statistic is 0.333, which corresponds to a medium effect size. The sample size is based on SD estimated from assays of human COPD lung tissues and nasal epithelial cells. The detectable fold-difference for primary and secondary analytes is listed in the table below. Estimates are also provided for a nominal type I error of 0.01 to account for multiple comparisons.

| Analyte      | Estimated SD
(Fold-change) | Effect Size (3 groups
of $n = 30$ , power =
0.80) |                 |
|--------------|-------------------------------|---------------------------------------------------------|-----------------|
|              |                               | alpha =
0.05                                         | alpha =
0.01 |
| Nrf2 protein | 0.198                         | 0.066                                                   | 0.080           |
| Nrf2 mRNA    | 1.007                         | 0.335                                                   | 0.406           |
| GTSM         | 0.397                         | 0.132                                                   | 0.160           |
| GSTP1        | 0.273                         | 0.091                                                   | 0.110           |
| HO-1         | 0.427                         | 0.142                                                   | 0.172           |
| NQO1         | 0.484                         | 0.161                                                   | 0.195           |

These effect sizes are highly plausible and have potential clinical importance insofar as they compare to changes of 1.25-4.00-fold in Nrf2 activity in control smokers vs. patients with COPD, and 2-3-fold changes in anti-oxidant enzymes induced by oral sulforaphane in control nasal epithelium. Tests for trend for these analytes vs. dose with 90 patients in 3 groups has 80% power with type I error of 0.05 to detect a correlation coefficient of 0.26 or greater.

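### The unadjusted ANOVA on fold-change is valid but forgoes precision: baseline is a covariate only after an undefined imbalance, and the log scale is not fixed

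*Protocol*

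**What the plan says.** Section 4.2 names the primary model: "The primary analysis will be an unadjusted one-way ANOVA for fold-change in Nrf2 expression and phase II antioxidant levels", with dose as the main effect. Two further sentences there bear on it. On covariates: "If significant imbalance occurs between groups, then general linear models will be constructed to adjust for baseline differences". On scale: "Appropriate transformations will be applied to data that is non-parametric". The first gives no definition of imbalance, no covariate list, and no statement of whether the adjusted model would replace or support the ANOVA. The second permits a log transform without fixing one.

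Section 2.5.1 defines the outcome as a within-person change: "The primary design variables are the change in Nrf2 expression in alveolar macrophages (AM) and bronchial epithelial cells (BEC"). Section 2.6 and Table 1 schedule BAL and bronchial brushing for each participant at V3 (day 0) and again at V5 (days 22 to 31), so a baseline level of each marker is planned.

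Section 4.1 sizes the trial on the same unadjusted model: "assuming 30 samples per each of 3 groups, and 80% power, the detectable effect size by Cohen's" f statistic is 0.333. It also lists a fold-change SD for each of six analytes, from 0.198 (Nrf2 protein) to 1.007 (Nrf2 mRNA).

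**The concern.** Fold-change uses the baseline level only as a denominator. On the log scale this fixes the slope of follow-up on baseline at 1. When the true slope is below 1, part of the baseline variation stays in the outcome as noise, because low baselines tend to give large ratios. A regression that estimates the slope removes it.

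The imbalance clause does not recover this. Imbalance between randomised arms is a chance event. Whether it occurs says nothing about how strongly baseline predicts follow-up, and that is what determines the gain from adjustment. The clause also leaves unclear which result the trial would stand on if both models were run.

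Scale is a separate matter. A ratio cannot be negative, so an SD of 1.007 around values near 1 implies marked right skew for Nrf2 mRNA. Analysing that ratio untransformed would lose power.

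At stake are precision in a trial with 30 patients per arm, and clarity about the primary result.

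**Working it through.** **Inputs from the protocol.** Three groups of 30, N = 90; power 0.80; alpha 0.05; f = 0.333; fold-change SDs from the table (section 4.1). Primary model from section 4.2.

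**Assumptions.** The correlation rho between log baseline and log follow-up is not given; the range 0.3 to 0.9 is shown. Log-scale variances are equal at the two visits unless stated otherwise. The true effect is held at f = 0.333 in units of the SD of log change.

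**1. The plan's own figure.** One-way ANOVA with F on (2, 87) degrees of freedom and noncentrality N f² = 90 × 0.333² = 9.98 gives power 80.0%. Solving for 80% power gives f = 0.3329 at alpha 0.05 and 0.4034 at alpha 0.01. All 12 table entries follow as f × SD, for example 0.3329 × 0.198 = 0.066 and 0.3329 × 1.007 = 0.335. The stated figures are right.

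**2. Variance under each model.** With log-scale variance s² at each visit:
- change score: 2(1 − rho)s²
- ANCOVA residual: (1 − rho²)s²
- ANCOVA relative to change: (1 + rho)/2

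The effective f for ANCOVA is therefore 0.333/√((1 + rho)/2), tested on (2, 86) degrees of freedom.

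| rho | Variance relative to change | Effective f | Power | N for 80% power |
|---|---|---|---|---|
| Planned ANOVA | 1.00 | 0.333 | 80.0% | 90 |
| 0.3 | 0.65 | 0.413 | 94.1% | 60 |
| 0.5 | 0.75 | 0.385 | 90.5% | 69 |
| 0.7 | 0.85 | 0.361 | 86.4% | 78 |
| 0.8 | 0.90 | 0.351 | 84.2% | 84 |
| 0.9 | 0.95 | 0.342 | 82.1% | 87 |

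Simulation (4,000 trials per setting) gave ANCOVA power of about 0.94, 0.90 and 0.86 at rho 0.3, 0.5 and 0.7. Type I error was about 0.04 to 0.06 for every method.

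**3. Where the gain disappears.** The log-scale slope is rho × (SD at follow-up / SD at baseline). If the SD ratio is 1.25 and rho is 0.8, the slope is 1.25 × 0.8 = 1 and ANCOVA power is 80.0%, no better than the plan. At the same SD ratio with rho 0.3, 0.5 and 0.7 it is 89%, 85% and 81%.

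**4. The imbalance rule.** Taking a significant imbalance to mean p<0.05 in a baseline comparison (an assumption), adjust-if-imbalanced had simulated power of 0.80 to 0.81 at rho 0.3 to 0.7, so almost all of the gain is lost.

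**5. Scale.** Take each listed SD as that of a log-normal ratio with mean near 1 (an assumption), so that the log SD is √ln(1 + SD²). For Nrf2 mRNA this is √ln(1 + 1.007²) = √ln 2.014 = 0.84. With the effect sized for 80% power on log fold-change, simulated power on the raw ratio is about 65% for Nrf2 mRNA and roughly 75 to 80% for the other five analytes.

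**6. Sensitivity to the source of the SDs.** Section 4.1 says: "The sample size is based on SD estimated from assays of human COPD lung tissues and nasal epithelial cells". If these are between-person SDs rather than SDs of change, power for change versus ANCOVA is 65% versus 84% at rho 0.3, 80% versus 90% at rho 0.5, and 96% versus 98% at rho 0.7. ANCOVA stays ahead.

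**The case against.** The plan contains no arithmetic or validity error here. Unadjusted ANOVA on change is sound in a randomised trial, the sample size is built on that model, and regression to the mean adds variance without biasing the comparison of arms. That stands in full.

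Details such as the transformation and the covariate list commonly belong in an SAP, which may exist. This stands for the scale, which is best described as open. It does not dispose of the main point, because the protocol itself names the unadjusted model as primary and makes adjustment conditional.

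Several stronger readings are tempting but not supported:

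- A reader might infer that a formal baseline test decides the model. Section 4.2 names no test; p<0.05 in step 4 is only a working definition.
- A reader might infer that the adjusted model would replace the primary analysis. The text does not say so, and a supportive analysis is an equally available reading. What can be said is that its status is unstated.
- A reader might conclude that the trial is underpowered for what it expects. Section 4.1 cites 2 to 3-fold enzyme changes in control nasal epithelium. With equal dose steps, f = 0.333 corresponds to a placebo-to-high difference of 0.333 × √6 = 0.816 SD, which is about 0.35 for HO-1 (0.816 × 0.427) and 0.39 for NQO1 (0.816 × 0.484). Both are well below a doubling, though Nrf2 mRNA is tighter at 0.82.
- A reader might take the raw-ratio loss as the expected power of the plan. It arises only if the promised transformation is not made, and it is large for one analyte of six.

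Finally, both bronchoscopies are scheduled, not guaranteed: section 4.2 allows removal of patients not healthy enough for the procedure. This limits any paired analysis, including the planned one.

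**Conclusion.** The point holds as a weakness of efficiency and pre-specification. The planned ANOVA has the 80% power claimed. Pre-specified log-scale ANCOVA would raise this to between about 94% (rho 0.3) and 82% (rho 0.9) with the same patients, visits and effect. These figures rest on an assumed rho, equal log-scale variances and a common linear baseline slope. Under a common slope the ANCOVA residual variance is never the larger, so the downside is confined to one degree of freedom, while the gain can be close to nothing if the slope is near 1. The conditional clause captures almost none of the gain and leaves the role of the adjusted result undefined. Fixing the log scale protects mainly Nrf2 mRNA. The change should be made because it is nearly free; the existing design does not fail without it.

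**What to change.** In section 4.2, and in the SAP if there is one:

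- Make the primary analysis, for each marker and cell type, an ANCOVA of log follow-up level on treatment arm with log baseline level as covariate.
- Report geometric-mean ratios of each dose versus placebo with 95% confidence intervals.
- Delete the sentence that makes adjustment depend on observed imbalance.
- Fix the log transform in advance.
- Keep the unadjusted one-way ANOVA on log fold-change as a sensitivity analysis.

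The existing sample size can stay, since it is conservative for the new model under the assumptions above. The cost is one degree of freedom (86 instead of 87 for error), a slightly less simple presentation, and protocol wording. No new data or procedures are needed.

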## Abstract

Chronic Obstructive Pulmonary Disease (COPD) is a major cause of morbidity and mortality in the United States and is a growing cause of chronic disease internationally. Presently, there are limited treatment options for this disease to modify the progression of airflow obstruction and decrease periodic exacerbations. Recent evidence has emphasized the central role of oxidative stress as a mechanism of COPD pathobiology. Evidence from our group has shown that COPD patients and animals exposed to cigarette smoke have impairment of antioxidant defenses which are caused by a defect in activity of Nrf2, a prolific regulator of anti-oxidant enzymes, glutathione homeostasis, and cytoprotective proteins. Activation of Nrf2 protects mice with chronic smoke exposure from developing emphysema, decreases oxidative stress, increases proteasomal anti-apoptotic cytoprotective responses, improves bacterial phagocytosis and killing, and reverses tobacco-smoke induced corticosteroid resistance. Similarly, *in vitro* Nrf2 activation in human COPD lung cells has shown improved cytoprotection, improved bacterial clearance, and restoration of steroid sensitivity. This trial focuses on sulforaphane, a derivative of cruciferous vegetables, which is a potent *in vitro* and *in vivo* stimulator of Nrf2 activity. We want to investigate whether ingestion of sulforaphane by COPD patients will increase Nrf2 activity and expression of downstream antioxidants in alveolar macrophages and bronchial epithelial cells. Accordingly, we are conducting a placebo-controlled randomized proof of principle trial of two oral doses of sulforaphane, 25 and 150 micromoles, for 4 weeks in 90 COPD patients. Collections of alveolar macrophages by BAL, bronchial epithelial cells by endobronchial brushings will be performed at baseline and 4 weeks. Other biospecimens will include nasal epithelial cells, Peripheral Blood Monocyte Collection (PBMCs), and expired breath condensate (EBC). Our goal is to establish a safe and tolerable dose of sulforaphane that effects *in vivo* antioxidants via Nrf2, then we will have a novel candidate treatment for longer-term efficacy trials. Ancillary studies are proposed to explore the efficacy and mechanisms of sulforaphane to increase bacterial clearance and to restore steroid sensitivity in COPD lung cells.

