### **1.5 Objectives**

The primary goals of this trial are to:

- Establish proof of principle -- Does oral sulforaphane increase Nrf2 expression and downstream anti-oxidant enzymes in lung macrophages and epithelial cells.
- Determine tolerability and dose-ranging for subsequent clinical research
- Establish non-invasive surrogate biomarkers for Nrf2 expression in the lung
- Conduct ancillary mechanistic studies to determine whether *in-vivo* treatment increases bacterial phagocytosis and killing and decreases corticosteroid resistance

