#### **2.5.2 Secondary outcome**

Supportive secondary outcome measures will include measures of oxidant stress from plasma and expired breath condensate. We will also conduct ancillary exploratory studies to determine whether the treatment improves function of alveolar macrophages in bacterial clearance and improves steroid sensitivity. Markers of oxidative stress include 8-isoprostane,  $H_2O_2$ , GSH/GSSG, Nitrotyrosine, Protein carbonyls, TBARS

1. Measures of oxidative stress. Oxidant stress indicators (isoprostane) will be measured in plasma and expired breath
2. Measures of airway inflammation will be measured as BAL cell counts and cytokine profiles
3. Pulmonary function tests including spirometry will be measured to determine whether there are any short-term functional effects of the treatment.
4. Patient Reported Outcomes will include the MRC dyspnea scale and SGRQ which includes questions on cough and sputum production. Adverse events will include both spontaneous reports as well as targeted symptoms related to respiratory and GI systems. Adverse events will be scored based on the NCI Common Toxicity Criteria rating scale.
5. Safety Measures will include baseline (V1) and follow-up (V4) CBC and biochemical profile including renal function, thyroid function, and liver function tests. Women of childbearing potential will have a pregnancy test at V1 and V4.

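### The multiplicity-adjusted p-value rule for secondary outcomes makes no exception for adverse events and safety laboratory tests, which lowers sensitivity to harm

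*Protocol*

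**What the plan says.** All references are to the protocol.

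- **Classification.** The section headed "2.5.2 Secondary outcome" is a numbered list. Within item 4, after the patient-reported outcomes, it says "Adverse events will include both spontaneous reports as well as targeted symptoms related to respiratory and GI systems". Item 5 reads "Safety Measures will include baseline (V1) and follow-up (V4) CBC and biochemical profile including renal function, thyroid function, and liver function tests". These stand beside oxidative stress, airway inflammation and lung function.
- **Analysis rule.** Section 4.2 sets the primary analysis: "The primary analysis will be an unadjusted one-way ANOVA for fold-change in Nrf2 expression and phase II antioxidant levels", with Tukey comparisons between doses and a test for trend. The next paragraph covers the rest: "Secondary outcome measures will be similarly analyzed, but p-values will be adjusted for multiple comparisons". Safety is not set apart, and neither the adjustment method nor the family of comparisons is named.
- **Aim.** The Abstract says "Our goal is to establish a safe and tolerable dose of sulforaphane". Section 1.5 has, among the primary goals, "Determine tolerability and dose-ranging for subsequent clinical research".
- **Size.** Section 4.1 gives power only for the analytes, "assuming 30 samples per each of 3 groups, and 80% power". It adds a column at alpha 0.01 as its allowance for multiple comparisons.

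**The concern.** Multiplicity adjustment protects against false positive claims. That is the right protection for a list of biomarkers, any of which might be put forward as a benefit. For harms the costlier error is usually the missed signal, and adjustment increases that error. It also makes the threshold for a liver enzyme or an adverse event depend on how many cytokines and oxidative stress markers happen to share its family.

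Tolerability by dose is meant to inform later trials. The only formal between-arm comparison that the protocol describes for safety data is one that has been made less sensitive, in a trial whose arms are already small for this purpose.

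**Working it through.** **Inputs from the protocol.** Three arms of 30; alpha 0.05; alpha 0.01 as the multiplicity allowance (all section 4.1). Post-bronchoscopy fever in about 5% of patients (section 5.1), the only rate in the text that can serve as a base rate here.

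**Assumptions.** A 0.5 SD shift in one safety laboratory value, confined to one arm. Adverse event rates of 10% versus 30%, and of 5% versus 20%. The protocol gives no expected harms by arm. Using 0.01 as the adjusted level is also an assumption, since section 4.2 fixes no level, but it is the only allowance the protocol offers.

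**Step 1: reproduce the protocol's figure.** One-way ANOVA power is P(F' > F_crit), where F' is non-central F with 2 and 87 degrees of freedom and noncentrality λ = 90·f². Solving for 80% power gives f = 0.3329 at 0.05, which matches the stated 0.333. At 0.01 it gives f = 0.403. Multiplying the listed SDs by these two values reproduces all 12 entries of the section 4.1 table.

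**Step 2: safety laboratory value under the same ANOVA.** With arm means of 0, 0 and 0.5 SD, the grand mean is 0.1667 and the squared deviations sum to 2(0.1667²) + 0.3333² = 0.1667. So λ = 30 × 0.1667 = 5.0.

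| Alpha | F_crit (2, 87) | Power | Missed |
|---|---|---|---|
| 0.05 | 3.10 | 0.489 | 51% |
| 0.01 | 4.86 | 0.255 | 74% |

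**Step 3: adverse events.** One active arm against placebo, 30 per arm. Exact power of the two-sided Fisher test is the sum of the binomial probabilities of all tables with p ≤ alpha.

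| Rates | Power at 0.05 | Missed | Power at 0.01 | Missed |
|---|---|---|---|---|
| 10% vs 30% | 0.372 | 63% | 0.149 | 85% |
| 5% vs 20% | 0.241 | 76% | 0.075 | 93% |

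Fisher's test is used because ANOVA suits counts of events poorly. A simulated three-arm ANOVA on 0/1 data with rates of 5%, 5% and 20% gives power 0.46 at 0.05 and 0.25 at 0.01, so the same loss appears with the test as literally written.

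**Step 4: separate the two causes.** For the laboratory shift, 51 points of the 74 are present at 0.05 and about 23 are added by moving to 0.01. For 10% versus 30%, 63 of the 85 are present and about 22 are added. The rule causes the added part; the sample size causes the rest.

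**Step 5: what estimation would show.** With no events among 30 patients, the one-sided 95% upper limit is 1 − 0.05^(1/30) = 9.5%. A confidence interval puts that uncertainty on the page; an adjusted non-significant p-value does not.

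**The case against.** The strongest objection is that the reading is too literal. The primary analysis is an ANOVA on fold-changes, which fits continuous analytes and not graded adverse event reports. Adverse events appear as a run-on within the patient-reported outcomes item, and item 5 carries its own label as safety measures. The authors may never have meant the adjusted tests for these data. This has weight: the reading is firmer for continuous laboratory values than for adverse events. But both sit in the secondary outcome list, and section 4.2 exempts neither.

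Second, other safeguards exist. Section 4.2 has outcome measures examined descriptively and graphically, adverse events are graded, and section 4.3 gives an independent board the review of serious events, including those that require permanent discontinuation. This stands. None of it depends on an adjusted p-value, so the rule is not the trial's only source of safety information.

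Third, an analysis plan that is not shown may contain a fuller safety analysis. The absence of margins or intervals from a protocol is therefore no fault in itself. The point here is narrower: the protocol states a rule that covers safety data. An analysis plan that follows it inherits the problem, and one that departs from it contradicts the protocol.

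A reader might also infer three stronger things that the text does not support:

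- **That a non-significant test will be read as showing safety.** The protocol nowhere says so.
- **That the plan is plainly stricter on harm than on benefit.** The primary markers have Tukey control and a 0.01 planning column, proof of principle needs Nrf2 plus at least two enzymes (section 2.5), and the adjustment falls equally on efficacy-type secondary outcomes.
- **That safety is a listed primary goal.** Section 1.5 names tolerability and dose-ranging; the reference to a safe dose is in the Abstract.

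**Conclusion.** The point holds as a flaw in a stated rule. Sections 2.5.2 and 4.2 together place adverse events and safety laboratory tests under multiplicity-adjusted testing, and this lowers sensitivity to harm. At 0.01 instead of 0.05, the chance of missing a 0.5 SD laboratory shift rises from 51% to 74%, and that of missing 10% versus 30% rises from 63% to 85%.

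These figures rest on assumed effects and on 0.01 as the adjusted level. A Bonferroni correction over ten or more outcomes would give higher miss rates, but the protocol specifies neither that method nor that family. The loss concerns small and moderate harms. By the normal approximation for two arms, a rise from 5% to about 33% would reach 80% power at 0.05. The larger share of each miss rate comes from having 30 per arm, and changing the rule will not remove it.

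**What to change.** In section 4.2, after the sentence on secondary outcomes, add text to this effect: adverse events and safety laboratory measures are exempt from the adjusted p-value rule. For these, report per-arm counts or means, and each dose minus placebo with an unadjusted 95% confidence interval, exact for event rates. A non-significant difference is not to be taken as evidence of safety. Keep the adjustment for the efficacy-type secondary outcomes.

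The cost is one or two sentences, with no new data and no additional patients. The downside is a few more chance safety signals to interpret, and intervals that will look wide at this sample size.

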## 2.6 Study Data Collection schedule

The specific study procedures and approximate time commitment from the participant are shown below:

Participants will have 5 study visits over 4-8 weeks as follows:

Visit 1 (V1) (Day – 28 to -7) (2 hours) During this visit, the participant will provide informed consent, undergo eligibility screening questionnaire, lung function (spirometry before and after bronchodilators), Complete Blood Count, biochemistry panel including renal and liver function and electrolytes, TSH, urinalysis, and a pregnancy test for women of child-bearing potential.

Visit 2 (V2) (Day -14 to 0) (2-4 hours) During this visit, eligible participants will perform baseline spirometry, lung volumes, and diffusing capacity, and will complete general health questionnaires and respiratory specific questionnaires (ATS-DLD, SGRQ and MRC). A brief physical examination will be performed. Baseline biological specimens including blood for PBMCs will be performed.

Visit 3 (V3) (Day 0) (4 hours) The participant will have a baseline bronchoscopy for collection of bronchoalveolar lavage cells and nasal and bronchial epithelial brushings. Randomization eligibility will be established and the participant will be assigned to a masked treatment. After recovery from the bronchoscopy sedation, the participant will be given the assigned treatment which will consist of a coded container of capsules containing either placebo or one of the two doses of sulforaphane.

Phone Visit 1 (P1) (Day 1) (15-30 minutes) Patients are phoned the day following the bronchoscopy to determine whether they have had any adverse experiences, to re-instruct them in use of the medication, and to confirm future appointment dates and times.

Phone Visit 2 (P2) (Day 7-14) (15-30 minutes) Patients are contacted to determine their compliance with the medication and to report any adverse effects.

Visit 4 (V4) (Day 21 to 30) (2 – 4 hours) The participant will repeat the baseline spirometry, lung volumes and diffusion capacity, CBC, pregnancy test, urinalysis, TSH and biochemistry panel and have follow-up health status and adverse effect questionnaires and a brief physical examination. Follow-up collections of blood for biological measures are obtained.

Visit 5 (V5) (Day 22 to 31) (4 hours) Follow-up bronchoscopy for collection of bronchoalveolar lavage, nasal brushings, specimens and endobronchial brushings. Return of unused capsules for pill counts.

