### **3.4 Unmasking**

Drug and placebo will be supplied in similar appearing capsules, back-filled with methylcellulose to approximate similar appearance and weight. Neither the participant nor the site investigators or the laboratory personnel will know the identity of the drug assignment. Emergency unmasking can take place by opening a sealed envelope that is distributed with the drugs. All unmasking events are reported to the DCC. The sealed envelopes are returned to the DCC at the end of the trial. Also, the investigators doing the bioassays will do them masked to treatment assignment. It is our general position that unmasking of treatment assignment is rarely necessary. If adverse events occur that may be related to the study treatment, then the study treatment is stopped and the patient is followed on an intention to treat basis. Envelopes with treatment assignment are provided to the clinic in the case a treating physician feels it is important to know the treatment assignment.

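### The removal sentence in section 4.2 can be read to let a study-related adverse event alone end follow-up, against the stop-drug-and-follow rule in 3.4

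*Protocol*

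**What the plan says.** Three statements in the protocol govern what happens to a participant who has an adverse event or stops the drug.

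- **Section 3.4 (Unmasking).** For an adverse event that may be due to the study treatment, "then the study treatment is stopped and the patient is followed on an intention to treat basis".
- **Section 4.2, retention.** "Participants will continue to be enrolled in the trial regardless of whether they take the study medication", and the reason given is "as our first analysis will be an intention to treat analysis".
- **Section 4.2, removal, at the end of the same paragraph.** "Patients may be removed from the study if they sustain interim adverse events related to the study", then, after a comma and no conjunction, "if they are not healthy enough to undertake the study procedures (e.g. bronchoscopy".

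The outcome at stake is set in section 2.5.1: "The primary design variables are the change in Nrf2 expression in alveolar macrophages (AM) and bronchial epithelial cells (BEC". Section 2.6 and Table 1 place the only bronchoscopy after treatment at V5: "Follow-up bronchoscopy for collection of bronchoalveolar lavage, nasal brushings, specimens and endobronchial brushings". Table 1 places the follow-up spirometry, lung volumes, blood count, chemistry, TSH, urinalysis, breath condensate, research blood, SGRQ/MRC and health status/adverse event form at V4.

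**The concern.** Two of the three statements keep the participant in the trial after the drug is stopped. The third, on one natural reading, lets the same participant be taken out altogether. Three sites apply this text, and data that are never collected cannot be recovered at analysis.

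Someone removed before V5 has no primary outcome. Someone removed before V4 also has no follow-up safety laboratory values, although tolerability and dose-ranging are among the goals in section 1.5. If the event is caused by the drug, removal is an exclusion after randomisation whose frequency can depend on dose, in a trial that compares doses.

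**Working it through.** **1. The text, under each reading**

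| Case | Section 3.4 | 4.2, retention sentence | 4.2, removal sentence: separate grounds | 4.2, removal sentence: joint condition |
|---|---|---|---|---|
| Drug-related event, fit for bronchoscopy | stop drug, follow | stays | may be removed | stays |
| Drug-related event, unfit for bronchoscopy | stop drug, follow | stays | may be removed | may be removed |
| Bronchoscopy-related event, fit for a second one | not addressed | addresses only whether drug is taken | may be removed | stays |

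On the first reading, row 1 is a direct conflict. On the second, row 1 disappears but row 2 remains: 3.4 requires follow-up, and nothing measured at V4 needs a bronchoscope.

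**2. The plan's own figure**

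Inputs from section 4.1: three groups of 30, alpha 0.05, Cohen's f = 0.333, power 80%. The noncentrality is λ = N f² = 90 × 0.333² = 9.98 with 2 and 87 degrees of freedom, which gives power 0.800. The stated figure reproduces.

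For equally spaced means 0, d/2, d (an assumed pattern), the variance of the means is d²/6. So f = d/√6 and d = 0.333 × √6 = 0.816 SD between high dose and placebo.

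**3. Size if participants are removed**

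The protocol gives no removal rate. Assume k = 1, 2 or 3 of 30 are affected in the 150 micromole arm and none elsewhere.

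- *Removed, with the same response as those who stay.* Group sizes are 30, 30 and 30 − k. With λ = Σ nⱼ(μⱼ − μ̄)², power is 0.793, 0.785, 0.777.
- *Removed, and they would have responded differently by δ SD (assumed).* The high-dose mean shifts by (k/30) × δ. The last column is the false-positive rate when there is no true effect.

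| δ | k | Shift (SD) | Share of 0.816 | False-positive rate |
|---|---|---|---|---|
| 0.5 | 1 | 0.017 | 2.0% | 0.050 |
| 0.5 | 2 | 0.033 | 4.1% | 0.052 |
| 0.5 | 3 | 0.050 | 6.1% | 0.053 |
| 1.0 | 1 | 0.033 | 4.1% | 0.052 |
| 1.0 | 2 | 0.067 | 8.2% | 0.056 |
| 1.0 | 3 | 0.100 | 12.3% | 0.064 |

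The direction of the shift cannot be known.

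**4. Size if they are kept off drug**

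Assume full return to baseline by V5. The high-dose mean becomes d × (1 − k/30), a dilution of 3.3%, 6.7% and 10.0%. Power is 0.766, 0.734, 0.699 by simulation (40,000 trials, including the extra variance from mixing responders and reverted participants), or 0.771, 0.741, 0.708 by noncentral F with constant SD.

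**The case against.** The best defence is that the sentence is a safety rule with poor punctuation. Read jointly, it covers only people who cannot safely have a second bronchoscopy. The retention sentence concerns non-adherence and 3.4 concerns stopping drug, so neither speaks to unfitness for procedures. This stands in part. The joint reading is available, and it removes the sharpest conflict. It does not explain why the person, and not just the procedure, must leave.

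Second, the triggers differ: 3.4 refers to the treatment, 4.2 to the study. The wider term takes in bronchoscopy complications, the only source of events that the protocol quantifies (section 5.1: fever about 5%, infection about 0.5%). The baseline bronchoscopy precedes the first dose, so its direct complications need not vary by arm, and section 3.3 expects few drug effects. This stands as a limit on size. The wider term still includes treatment-related events, so the rules still meet there.

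Third, for someone truly unfit for V5, no rewording recovers the primary outcome. That is correct. For them the gain is confined to data that need no bronchoscope.

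Fourth, keeping participants costs more power than removing them (77-70% against 79-78%). That is also correct under the stated assumptions, and it is the price the protocol accepts by promising an intention to treat analysis.

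**Conclusion.** The concern holds in a limited form. The last sentence of 4.2 is open to a reading that contradicts 3.4 and the retention sentence. On the narrower reading it still ends all follow-up where omitting one procedure would do. What is lost is the V5 bronchoscopy where it was still feasible, and the scheduled V4 laboratory tests, blood, breath condensate, spirometry and questionnaires. The loss can differ by dose only for drug-related events.

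The likely effect is small: 1 to 2 points of power, and a shift of 0.02 to 0.10 SD. The 6.4% false-positive rate needs the extreme case of 3 of 30 removed in one arm only, all differing by 1 SD. Every count and response difference here is assumed.

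Three stronger readings are tempting, and the document does not support them.

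- *That the protocol requires removal for any related event.* The wording is permissive, and its second clause may narrow it.
- *That adverse events leading to removal would go untracked.* Section 4.3 counts an event that forces permanent cessation of treatment as serious, with follow-up reports until it ends. Most such events would therefore still be reported; the gap is the scheduled V4 assessments.
- *That the phrase "The primary analysis will use the modified intention to treat paradigm" shows removed participants will be dropped.* Defining that set is commonly left to the statistical analysis plan, which is not at hand. It has no bearing on whether sites should stop collecting data.

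**What to change.** In section 4.2 only, replace the removal sentence with:

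> An adverse event may lead to stopping study treatment but not to removal from the study. Participants who stop treatment still attend V4 and V5; a procedure such as the V5 bronchoscopy is omitted only if the investigator judges it unsafe or the participant withdraws consent, and the remaining procedures are still done.

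Section 3.4 already says the right thing and needs no change. The new wording adds no visits or assays, and investigators keep discretion over the drug and over unsafe procedures. The cost is a few off-drug V5 specimens, which dilute the high-dose effect by 3.3-10.0% under the assumed counts with full reversion. The secondary analysis of adherent patients already planned in 4.2 complements the intention to treat result.
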